## 2. Materials and Methods

### 2.1. Study Design and Setting

This multicenter, prospective, single-arm interventional implementation study will be conducted at 15 Chinese centers representing different levels of healthcare delivery: four tertiary Grade A hospitals, five secondary hospitals, and six primary-level hospitals. Chinese PLA General Hospital is the coordinating center.

The participating centers must have access to the target population; a designated local study team, the capacity to complete standardized multidimensional assessment and longitudinal follow-up; the ability to deliver or coordinate the core intervention domains; and the capacity to comply with common training, case report forms, fall surveillance, data quality, safety reporting, and ethical requirements. These minimum operational requirements are intended to preserve a common implementation standard across settings.

Including different levels of care is intentional and will allow for evaluation under real-world variations in case mix, staffing, rehabilitation capacity, equipment, and service organization. All centers will use the same eligibility criteria, assessment and intervention-assignment framework, outcome definitions, monthly fall surveillance schedule, documentation, training, and safety procedures. Specific intervention modalities may vary with participant-level clinical indications and local resources, but the underlying assessment and decision framework will remain standardized.

All participants will enter the same integrated pathway. There is no concurrent control arm, treatment allocation, or masking because the interventions are assigned based on a prespecified risk assessment and clinical indications.

The pathway comprises screening and consent, standardized baseline assessment; risk stratification; individualized multicomponent care; monitoring; reassessment; and adjustment according to response, adherence, safety, and changing risk. The follow-up will last 6 months (Figure 1; Table 1).

Figure 1 summarizes the screening, baseline assessment, risk stratification, individualized multicomponent intervention, monitoring and adjustment, 6-month outcome assessment, and integrated clinical and RE-AIM evaluation.

The protocol follows relevant prospective study-reporting principles and SPIRIT guidance [15,16].

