### 2.11. Follow-Up, Fall Ascertainment, and Dynamic Adjustment

Participants will be followed for 6 months using a standardized fall surveillance schedule across all centers, with structured contacts at Months 1, 2, 3, 4, and 5 and a final assessment at Month 6. Contacts may be conducted in person, by telephone, or by video according to accessibility; however, the surveillance interval, core questions, fall definitions, and event documentation procedures will be identical across centers. Additional clinical contacts may occur according to need but will not replace the scheduled surveillance.

The 6-month period was selected a priori to balance clinically meaningful prospective observation with feasibility in a multicenter implementation study. It permits estimation of 6-month toileting-related fall occurrence together with short-term changes in urinary symptoms, nocturia, mobility, functional independence, fidelity, safety, and follow-up performance. The monthly structured surveillance is intended to reduce recall-related underreporting; the study is not designed to establish long-term preventive effectiveness, recurrent fall risk beyond follow-up, or long-term organizational sustainability.

At enrollment, participants and/or caregivers will be instructed to record and promptly report any fall during follow-up. At each monthly contact, investigators will use a standardized surveillance form to determine whether a fall occurred since the previous contact and will document the date; relationship to going to, using, transferring on or off, or returning from the toilet; nighttime occurrence; location and circumstances; resulting injury; and assistance available at the time.

A fall is an event in which a participant unintentionally comes to rest on the ground, floor, or another lower level. Toileting-related falls will use the prespecified primary outcome definition. Caregivers may assist in reporting when participants cannot report reliably. Events reported between scheduled contacts will be reconciled at the next contact to avoid duplication.

Missed monthly contacts will be completed as soon as feasible and documented. At Month 6, all fall records will undergo a final completeness and classification review.

Care plans may be modified for new risks, symptom change, poor adherence, adverse events, or changes in function or care environment; major modifications and reasons will be documented.

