#### 2.12.3. Prespecified RE-AIM Implementation and Safety Outcomes

Reach: Enrollment rate among eligible screened individuals at completion of recruitment.Adoption: Proportion of centers completing initiation requirements and starting enrollment.Adoption: Proportion of designated personnel completing standardized protocol training before study procedures.Implementation: Completion rate of required and clinically applicable baseline assessments.Implementation: Proportion receiving ≥1 documented risk-matched individualized intervention during follow-up.Implementation: Risk–intervention concordance and predefined fidelity deviation frequency during follow-up.Implementation: Completeness of required baseline, intervention, and follow-up data at Month 6.Maintenance: Participant 6-month follow-up completion rate.Maintenance: Proportion of centers continuing protocol-based pathway delivery and follow-up through the 6-month study period.Safety: Proportion experiencing ≥1 adverse event judged as related or possibly related to a study intervention during follow-up.

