### 2.13. Safety Assessment and Adverse Event Reporting

Safety will be monitored throughout follow-up. For each adverse event, investigators will record the type, onset, severity, duration, management, outcome, and relationship to study intervention. Serious events will be managed according to clinical need and reported as required; device-related events or deficiencies will also be documented.

Serious adverse events will be reported to the sponsor, ethics committee, and relevant institutional authorities in accordance with applicable requirements.

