The study also has important limitations. The absence of a concurrent control group prevents causal attribution of changes in fall outcomes or functional measures to the integrated program. Observed within-participant changes may reflect the intervention, natural recovery or deterioration, regression to the mean, concurrent clinical care, or other time-related factors; clinical outcomes will therefore remain exploratory and hypothesis-generating. Participants will intentionally be heterogeneous in age, disability or functional impairment, comorbidity, urinary symptoms, mobility, care setting, caregiver support, and intervention exposure. The prespecified subgroup analyses will characterize this heterogeneity descriptively rather than confirm differential effects. In addition, participants may receive different combinations and intensities of urinary, rehabilitation, psychological/cognitive, caregiver, and environmental interventions; consequently, any observed clinical change cannot be reliably attributed to a single component of the pathway. Fall ascertainment may remain vulnerable to incomplete reporting despite the monthly structured surveillance, and not all symptom or functional instruments will be applicable to every participant. Variations in staffing, equipment, rehabilitation capacity, case mix, and local service organization may also contribute to inter-center differences in delivery. The common core protocol, standardized training and documentation, uniform surveillance, prespecified assignment criteria, and center-level fidelity monitoring are intended to limit this variability, but the center and center-type findings will remain descriptive rather than confirmatory.

If the integrated pathway demonstrates acceptable implementation, fidelity, safety, and follow-up performance, subsequent research should evaluate its effectiveness using comparative designs, such as pragmatic controlled or cluster-randomized studies and should examine the cost, resource use, sustainability, and the contribution of individual intervention components. The anticipated findings will be relevant to care delivered jointly by urology, rehabilitation medicine, nursing, psychology, geriatrics or primary care and community or long-term care services. Coordinated multidisciplinary implementation is therefore a central feature of the program rather than an ancillary component.

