## Figures and Tables

**Figure 1 healthcare-14-02794-f001:**
[figure not shown]
Overall study flowchart and technical roadmap.

**Table 1 healthcare-14-02794-t001:** Schedule of enrollment, intervention, and follow-up assessments.

Study Activity	Screening/Baseline	Intervention and Dynamic Management (0–6 Months)	Six-Month Assessment
Written informed consent	●		
Eligibility screening	●		
Demographic and medical history	●		
Multidimensional baseline assessment	●		
Risk stratification and individualized care plan	●	Review and adjustment	
Urinary symptom/nocturia management		As indicated	Review
Gait, balance, and physical rehabilitation		As indicated	Review
Psychological/cognitive support		As indicated	Review
Environmental and caregiver intervention		As indicated	Review
Fall and toileting-related fall surveillance		Ongoing	Final verification
Adherence and intervention delivery monitoring		Ongoing	●
Adverse event monitoring		Ongoing	●
OABSS	●		●
Nocturia episodes/voiding record	●	As clinically indicated	●
Tinetti Performance-Oriented Mobility Assessment	●		●
Modified Barthel Index	●		●
Implementation outcome assessment		Ongoing	●

Note: The symbol ● indicates a prespecified assessment or procedure at the corresponding study stage. The intervention components are selected according to individual risk factors and clinical indications; not every participant receives every component. OABSS, Overactive Bladder Symptom Score.

**Table 2 healthcare-14-02794-t002:** Operationalization of the RE-AIM framework in the present study.

RE-AIM Domain	Operational Definition	Prespecified Measures	Data Source/Time Point
Reach	Extent to which eligible individuals enter the integrated care pathway	Enrollment rate: Number enrolled/number of eligible screened individuals; distribution of enrolled participants by recruitment setting and key demographic/clinical characteristics	Screening and enrollment logs; recruitment period
Effectiveness	Exploratory clinical and safety outcomes observed during participation in the pathway	Proportion experiencing ≥1 toileting-related fall; nighttime toileting-related falls; total falls; change in OABSS, nocturia episodes, Tinetti score, and Modified Barthel Index; intervention-related adverse events	Baseline, prospective event surveillance, and Month 6 assessment

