Environmental	Lighting; route; handrails; non-slip measures; toilet height/bedside device adaptation	Multidisciplinary team, caregiver, or local service personnel	Required modification(s) and implementation timing	Match identified hazards, safety, and feasibility	Completion/non-completion and reason

**Table 5 healthcare-14-02794-t005:** Prespecified clinical, implementation, and safety outcomes.

Outcome Category	Outcome Measure	Time Frame
Primary	The 6-month cumulative incidence of at least one toileting-related fall	Up to 6 months after enrollment
Secondary	Number of nighttime toileting-related falls	Up to 6 months after enrollment
Secondary	Total number of falls from any cause	Up to 6 months after enrollment
Secondary	Change in OABSS	Baseline and Month 6
Secondary	Change in average nocturia episodes per night	Baseline and Month 6
Secondary	Change in Tinetti Performance-Oriented Mobility Assessment score	Baseline and Month 6
Secondary	Change in Modified Barthel Index	Baseline and Month 6
Reach	Enrollment rate among eligible screened individuals	At completion of recruitment
Adoption	Proportion of participating centers completing study initiation requirements and initiating participant enrollment	During the recruitment period
Adoption	Proportion of designated study personnel completing standardized protocol training	Before participation in study assessment or intervention delivery
Implementation	Completion rate of protocol-required and clinically applicable multidimensional baseline assessments	At baseline
Implementation	Proportion of participants receiving at least one documented individualized intervention matched to identified risk factors and clinical indications	Up to 6 months after enrollment
Implementation	Risk–intervention concordance rate	During the 0–6-month intervention period
Implementation	Proportion of participants with ≥1 predefined intervention fidelity deviation	Up to 6 months after enrollment
Implementation	Completeness of protocol-required study data	At Month 6
Maintenance	Six-month participant follow-up completion rate	At Month 6
Maintenance	Proportion of participating centers continuing protocol-based pathway delivery and follow-up for enrolled participants through completion of the 6-month study period	At completion of the 6-month study follow-up period
Safety	Proportion experiencing intervention-related or possibly related adverse events	Up to 6 months after initiation of intervention

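### The only prespecified safety outcome depends on causal attribution; serious adverse events regardless of cause and fall injuries are recorded but have no outcome of their own

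*Protocol article*

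**What the plan says.** The safety outcome is fixed in three places of the protocol article, each time limited by attribution:

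- Section 2.12.3: "Safety: Proportion experiencing ≥1 adverse event judged as related or possibly related to a study intervention during follow-up".
- Table 5, the only Safety row: "Proportion experiencing intervention-related or possibly related adverse events".
- Table 2, Effectiveness row, where the safety item closes the list: "change in OABSS, nocturia episodes, Tinetti score, and Modified Barthel Index; intervention-related adverse events".

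On who judges, section 2.13 says that for each adverse event "investigators will record the type, onset, severity, duration, management, outcome, and relationship to study intervention". It describes no central or independent review of causality. Section 2.1 adds: "There is no concurrent control arm, treatment allocation, or masking because the interventions are assigned based on a prespecified risk assessment and clinical indications".

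More is recorded than the outcome uses. Section 2.13 states: "Serious adverse events will be reported to the sponsor, ethics committee, and relevant institutional authorities in accordance with applicable requirements". In section 2.11 the monthly surveillance form covers, for each fall, "location and circumstances; resulting injury; and assistance available at the time".

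Safety is named among the study aims in the Abstract and among the implementation objectives in section 2.2. The Discussion makes later comparative research conditional on it: "If the integrated pathway demonstrates acceptable implementation, fidelity, safety, and follow-up performance".

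**The concern.** A proportion limited to attributed events is only as sound as the attribution. Here there is no comparator to show the background rate of events, no masking, and a population with disability, functional limitation or care dependency in which most events have competing explanations. The limitations paragraph in the Discussion says that, without a concurrent control, changes in fall outcomes or functional measures cannot be causally attributed to the program. The protocol therefore disclaims attribution for effectiveness while making it the sole gateway to the safety result.

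At stake is the statement on safety at the end of the study. A serious event or an injurious fall that is judged unrelated would leave no trace in the safety outcome, although the data needed to describe it would be in the database.

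**Working it through.** The point rests on definitions, so the first step is to trace each type of event through the listed outcomes (sections 2.12.1 to 2.12.3, Table 5) and the analysis section (2.15).

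| Event | Recorded | Counts in a listed outcome |
|---|---|---|
| Adverse event judged related or possibly related, serious or not | Yes, 2.13 | Yes, in the safety proportion, not split by seriousness |
| SAE judged unrelated, other than a fall | Yes, 2.13 | None |
| Fall with injury, judged unrelated | Yes, 2.11 | Counted as a fall (total falls; also the primary and nighttime outcomes where they apply); the injury is not used |
| Fall without injury | Yes, 2.11 | Counted as a fall |

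Section 2.15 names no summary of SAEs regardless of cause and none of injurious falls. The gap is rows two and three.

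**The plan's own precision figures.** Section 2.14 gives maximum 95% half-widths for a proportion near 50%. With half-width = 1.96 × √(0.25/n):

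- n = 300: 5.66 points (stated 5.7)
- n = 270: 5.96 (stated 6.0)
- n = 255: 6.14 (stated 6.1)
- n = 240: 6.33 (stated 6.3)

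All four are reproduced. They neither support nor weaken the point.

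**What a favourable result would look like.** With no attributed event in 300, the exact two-sided 95% upper limit is 1 − 0.025^(1/300) = 0.0122, or 1.2%. The number of unattributed SAEs or injurious falls does not enter this calculation.

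**Illustration under assumed rates.** The documents give no SAE rate and no share judged related, so both are assumptions here. Let p be the proportion of 300 participants with an SAE of any cause, and s the share of those judged related.

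- Participants with an SAE: 300p.
- Half-width if all are counted: 1.96 × √(p(1 − p)/300).
- Expected number of them in the present outcome: 300ps.
- Chance that none of them is counted: (1 − ps)^300.

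| p | With an SAE | Half-width (points) | Counted now, s = 5% to 50% | Chance none counted, s = 5% |
|---|---|---|---|---|
| 5% | 15 | 2.5 | 0.75 to 7.5 | 47% |
| 10% | 30 | 3.4 | 1.5 to 15 | 22% |
| 20% | 60 | 4.5 | 3 to 30 | 5% |

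An outcome regardless of attribution would thus be estimated with useful precision at the planned size, whereas what the present outcome shows of the same events depends heavily on s, which nobody can check from the published result.

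**The case against.** The strongest reply is that this is ordinary content of a statistical analysis plan. The article condenses a fuller protocol, section 2.15 refers to a plan that is not shown, and tables of SAEs, deaths and injuries are commonly specified there. Nothing in the article forbids them. This is fair as far as it goes: unseen tables may exist. But the article is not merely silent. It presents its outcome list as prespecified and in three places chooses a safety endpoint limited by attribution. Extra tables elsewhere would not change that endpoint.

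Other parts of the reply stand and limit the point:

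- A reader might infer that SAEs and fall injuries enter no outcome at all. They do enter the safety proportion when judged related or possibly related, and every fall counts without attribution in the primary or secondary outcomes.
- A reader might infer that treating clinicians judge their own choice of intervention and attribute too little. Section 2.13 says only that investigators record the relationship, section 2.8 gives assignment to the multidisciplinary team, and no figure in the documents bears on how often events are attributed. The criterion also includes possibly related events, which is broad.
- A reader might infer that serious events would go unreported. Section 2.13 requires their reporting to the sponsor, the ethics committee and institutional authorities, and severity is recorded for every adverse event.
- The Discussion sets no threshold for acceptable safety, and the clinical outcomes are declared exploratory, so no formal decision rule hangs on this proportion.

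**Conclusion.** The point holds in a limited form. The sole safety outcome requires a causal judgement in a study without control or masking, with no independent review described. SAEs regardless of attribution, and the severity side of falls, have no place among the listed outcomes or analyses. The safety conclusion would therefore rest on attribution alone, with fall counts beside it that carry no information on injury.

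The size cannot be fixed from the documents. The 1.2% upper limit is correct arithmetic for a hypothetical result of zero attributed events in 300, and the table under assumed rates only shows how far the present outcome could diverge from a count regardless of cause. Neither is a forecast, and no bias in attribution is claimed. This is a worthwhile and cheap improvement to the outcome list, not a flaw that undermines the study.

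**What to change.** Keep the attributed proportion. Add to section 2.12.3 and Table 5, as descriptive safety outcomes:

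1. the proportion of participants with at least one SAE regardless of attribution, including fatal outcomes as recorded in the outcome field of the adverse event record;
2. the number and person-time rate of injurious falls, overall and toileting-related, using the injury item on the monthly form and the person-time approach that section 2.15 already applies to falls.

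Give the new lines one stated observation window. The existing safety outcome runs over follow-up in section 2.12.3 but from the start of intervention in Table 5, and the two should be reconciled in the same edit.

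The cost is a few table lines and a possibly less favourable safety summary. No new data item is needed, and no new rule on recording falls as adverse events is asked for, since that would change practice at 15 centers. The article reports that recruitment had not begun on 1 August 2026, so the change could be made before the first participant is enrolled.

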### 2.13. Safety Assessment and Adverse Event Reporting

Safety will be monitored throughout follow-up. For each adverse event, investigators will record the type, onset, severity, duration, management, outcome, and relationship to study intervention. Serious events will be managed according to clinical need and reported as required; device-related events or deficiencies will also be documented.

Serious adverse events will be reported to the sponsor, ethics committee, and relevant institutional authorities in accordance with applicable requirements.

### 2.14. Sample Size and Enrollment Target

A total of 300 participants are planned to be enrolled, consistent with the registered target. This target refers to participants enrolled and does not imply that all 300 will necessarily have evaluable 6-month outcome data because some loss to follow-up is anticipated.

Because the study is primarily designed to evaluate implementation of a complex individualized pathway rather than superiority of a single treatment against a concurrent control group, no treatment-effect-based sample size calculation was used. The pragmatic target supports multicenter implementation and reasonably precise estimation of key proportions. For an evaluable sample of 300, a simple binomial approximation gives a maximum 95% confidence interval half-width of about 5.7 percentage points for a proportion near 50%, with narrower intervals farther from 50%.

No cluster design effect inflation was applied because this is not a cluster-randomized comparative trial and a reliable intraclass correlation is unavailable. Center clustering will instead be addressed in the prespecified analyses, with center-specific estimates reported descriptively.

With a 10%, 15%, or 20% loss to follow-up, approximately 270, 255, or 240 participants would remain evaluable, corresponding to maximum 95% confidence interval half-widths of about 6.0, 6.1, or 6.3 percentage points for a proportion near 50%.

The numbers enrolled, completing follow-up, and included in each analysis will be reported with reasons for loss or non-evaluability. Center and subgroup analyses will be descriptive, not separately powered tests of differential effectiveness.

